## Abstract

**Background:**

Opioids accounted for 75% of drug overdoses in the USA in 2020, with rural states particularly impacted by the opioid crisis. While medication-assisted treatment (MAT) with Suboxone remains one of the more efficacious treatments for opioid use disorder (OUD), approximately 40% of people receiving Suboxone for outpatient MAT for OUD (MOUD) relapse within the first 6 months of treatment. We developed the smartphone app-based intervention OptiMAT as an adjunctive intervention to improve MOUD outcomes. The aims of this study are to (1) evaluate the efficacy of adjunctive OptiMAT use in reducing opioid misuse among people receiving MOUD and (2) evaluate the role of specific OptiMAT features in reducing opioid misuse, including the use of GPS-driven just-in-time intervention.

**Methods:**

We will conduct a two-arm, single-blind, randomized controlled trial of adults receiving outpatient MOUD in the greater Little Rock AR area. Participants are English-speaking adults ages 18 or older recently enrolled in outpatient MOUD at one of our participating study clinics. Participants will be allocated via 1:1 randomized block design to (1) MOUD with adjunctive use of OptiMAT (MOUD+OptiMAT) or (2) MOUD without OptiMAT (MOUD-only). Our blinded research statistician will evaluate differences between the two groups in opioid misuse (as determined by quantitative urinalysis conducted by clinical lab staff blinded to group membership) during the 6-months following study enrolment. Secondary analyses will evaluate if OptiMAT-usage patterns within the MOUD+OptiMAT group predict opioid misuse or continued abstinence.

**Discussion:**

This study will test if adjunctive use of OptiMAT improve MOUD outcomes. Study findings could lead to expansion of OptiMAT into rural clinical settings, and the identification of OptiMAT features which best predict positive clinical outcome could lead to refinement of this and similar smartphone app-based interventions.

**Trial registration:**

ClinicalTrials.gov
identifier: NCT05336188, registered March 21, 2022.

**Supplementary Information:**

The online version contains supplementary material available at 10.1186/s13063-023-07213-3.

## Administrative information

Note: the numbers in curly brackets in this protocol refer to SPIRIT checklist item numbers. The order of the items has been modified to group similar items (see http://www.equator-network.org/reporting-guidelines/spirit-2013-statement-defining-standard-protocol-items-for-clinical-trials/).

## Introduction

### Background and rationale {6a}

The USA is experiencing an opioid use crisis. Opioids were involved in 68,630 overdose deaths (over 188 people daily) in 2020, accounting for 75% of all US drug overdose deaths [1]. Rural states are particularly impacted by this growing crisis, as greater opioid dispensing rates and less accessibility to healthcare resources have resulted in opioid-related mortality rates up to four times greater than urban areas. As a rural state, Arkansas is no exception, having the second highest opioid dispensing rate in the nation (75.8 opioid prescriptions per 100 residents as compared to national average of 43.3 in 2020) [2].

The most efficacious therapy for opioid use disorder (OUD) is medication for OUD (MOUD) which uses opioid substitution (primarily methadone or buprenorphine) to alleviate craving and withdrawal symptoms to promote abstinence. Clinical trials have reported opioid abstinence rates as high as 75% during short-term inpatient MAT [3]. However, an estimated 60% of OUD patients relapse within 1 year of initiating outpatient MAT therapy [4]. Adjunctive medication therapies during MAT (such as extended-release naltrexone) help attenuate relapse rates (reducing rates to ~40%) [4, 5], but these adjunctive therapies likewise suffer from limited availability in rural areas.

Telemedicine has emerged as a potential solution to the geographic barriers limiting healthcare access in rural areas. Specifically, smartphone applications (“apps”) have been developed which administer brief motivational interventions to aid weight loss [6–9], smoking cessation [10–12], and alcohol use reduction [13–15]. These app-based interventions combine *self-monitoring* of caloric intake, exercise, or drug use with *personalized feedback* to shape users’ behavior. However, this technology has not been applied to OUD in rural states, where rates of OUD are increased relative to population size and MOUD access is limited by geographic and financial barriers.

Therefore, we developed OptiMAT (“Optimizing Medication-Assisted Treatment”), a novel app-based intervention to reduce opioid relapse during outpatient MOUD. OptiMAT provides: self-monitoring of daily opioid use, opioid craving, and mood; personalized feedback on MOUD goal attainment; charts depicting pattern of self-assessment responses over time; health promotion information, including identifying nearby abstinence-supporting resources; daily reminders to complete logging activities; and a GPS-driven just-in-time intervention. Since OptiMAT is an adjunctive intervention, we will compare outcomes of patients receiving outpatient MOUD with OptiMAT (MOUD+OptiMAT) against outcomes of patients receiving only outpatient MOUD (MOUD-only).

### Objectives {7}

The primary objective of this study is to evaluate whether a smartphone app-based adjunctive intervention (OptiMAT) can reduce opioid misuse among patients receiving MOUD. The secondary objectives are to evaluate the role of specific OptiMAT app features in reducing opioid misuse, including its use of GPS-driven just-in-time intervention.

### Trial design {8}

We will recruit patients with opioid use disorder who have initiated outpatient MOUD to participate in a two-arm stratified randomized control trial (RCT) to evaluate the superiority of the MOUD+OptiMAT intervention over MOUD-only. Participants will be randomized 1:1 within each stratum (comorbid chronic pain and comorbid use of alcohol and/or marijuana, as detailed below) to either the MOUD-only arm (treatment as usual) or the MOUD+OptiMAT arm (adjunctive treatment intervention).

Of note, participants from each study arm will also be invited to participate in a longitudinal functional neuroimaging substudy investigating neural mechanisms associated with recovery from opioid use disorder, to be conducted at the University of Arkansas for Medical Sciences (UAMS) Brain Imaging Research Center (BIRC). This neuroimaging substudy is not directly pertinent to the RCT methods and will be detailed in future publications.

## Methods: participants, interventions, and outcomes

### Study setting {9}

Participants will be recruited from outpatient MOUD clinics in the central Arkansas area. The primary study setting is the UAMS Psychiatric Research Institute (PRI). The primary recruitment site is the UAMS PRI Center for Addiction Services and Treatment (CAST) outpatient MOUD clinic. Secondary recruitment sites will be identified through treatment programs participating in the MATRIARC program (Medication-Assisted Treatment Recovery Initiative for Arkansas Rural Communities), a partnership between UAMS and the Arkansas Department of Human Services designed to expand evidence-based treatment for opioid use disorders.

### Eligibility criteria {10}

Inclusion criteria for the trial are males and females, 18 years of age or older, who have initiated outpatient MOUD at CAST or an affiliated MAT clinic within the past three weeks. The patient must have completed the initial Intake session and at least one of the weekly individual therapy sessions. The RCT study has no exclusionary criteria. Note that past MOUD treatment, including initiating MOUD in a residential setting prior to initiating outpatient MOUD, is not exclusionary.

### Who will take informed consent? {26a}

Research coordinators will obtain written informed consent from potential trial participants at the UAMS CAST clinic or UAMS MATRIARC-affiliated clinic. We have obtained a partial waiver of HIPAA authorization so that clinical staff may identify patients meeting eligibility criteria and introduce those individuals to a research coordinator embedded within CAST or UAMS MATRIARC programs. The research coordinator will provide patients with IRB-approved advertisements describing the study. The research coordinator will also schedule an intake visit for interested patients, where patients will undergo the informed consent process (including full HIPAA authorization) in a private and confidential setting. We have also obtained a partial HIPAA waiver so that participants who need more time to decide may provide us with contact information (i.e., name and phone number) so that we may contact them at a later date.

### Additional consent provisions for collection and use of participant data and biological specimens {26b}

This trial will not collect biological specimens. Biological specimens collected for clinical use (i.e., urinalysis) will not be stored or used for research. Consistent with Open Science principles, data collected from this trial will be de-identified and shared with neuroimaging data repositories. The informed consent form clarifies this data sharing process with the participant and that the shared de-identified data may be used for other purposes (e.g., methods development) beyond the scope of this trial.

### Interventions

#### Explanation for the choice of comparators {6b}

Since OptiMAT is an adjunctive intervention, we will compare opioid misuse outcomes of patients receiving outpatient MOUD with OptiMAT (MOUD+OptiMAT) against outcomes of patients receiving only outpatient MOUD (MOUD-only).

##### Control condition: MOUD-only

Participants randomized into the MOUD-only study arm will undergo treatment as usual (TAU) with Suboxone MOUD without adjunctive use of the OptiMAT smartphone app, as described above.

##### Experimental condition: MOUD+OptiMAT

Participants randomized into the MOUD+OptiMAT study arm will continue with MOUD treatment with adjunctive use of the OptiMAT smartphone app. Adapted from HealthCall-S [16], OptiMAT is a complementary relapse minimization intervention for MOUD providing (1) *self-monitoring* to promote awareness of opioid misuse and (2) *personalized feedback* for motivating abstinence goals. Pilot studies have shown HealthCall-S’s efficacy in reducing alcohol use with or without comorbid use of other drug of abuse [16–20]. Our choice of the HealthCall-S app as the adapted technology is further motivated by our preliminary data demonstrating its efficacy in reducing alcohol use and risky sexual behavior among homeless young adults [21].

##### Base features

Like its predecessors, OptiMAT consists of three features accessible to participants: (1) self-monitoring (aka “Tracker”), (2) personalized feedback (including “Graphs”), and (3) accessible resources. Geographical Ecological Momentary Assessment (GEMA) will not be directly accessible; this feature will run in OptiMAT’s background to record participants’ geospatial locations and intervene when participants enter individually defined high lapse-risk environments.(1) *Self-monitoring and (2) personalized feedback*. These features function interactively as brief interventions for reducing opioid use. Participants will be asked to complete daily assessments of (a) opioid use, (b) opioid craving, (c) withdrawal symptoms, (d) mood (stress, anger, and sadness), and (e) use of alcohol or marijuana. Participants will be asked to complete the assessments at their convenience and will receive daily reminders at a time they prefer. Self-ratings will consist of yes/no questions (for opioid, alcohol, and marijuana use) and number responses entered by either a number pad (for amount spent on opioids, number of beer equivalents, or number of times used marijuana) or a labeled sliding bar Likert scale (for craving, withdrawal, and mood scales). Participants will receive personalized feedback consisting of positive reinforcement for meeting abstinence goals or encouragement and tips to change behavior if lapsed to opioid use and/or experienced high opioid craving. Rating sessions will conclude with graphs summarizing responses, additional encouragement and restating of goal reminders, and further guidance from the Tip Bank. These response graphs will also be available to participants through the Graphs toolbox.(3) *Abstinence-promoting resources*. OptiMAT will provide personally targeted information to help participants maintain abstinence from opioid misuse, including (a) information to help manage withdrawal symptoms, such as encouragement that the symptoms will pass; (b) a Tip Bank with tips to reduce craving (such as distracting activities or guided relaxation); and (c) contact information for local emergency resources. Since our OnTrack study suggested participants will be unlikely to explore the Tip Bank on their own, the Tip Bank will provide additional lapse prevention guidance as part of the personalized feedback.

UAMS has recently initiated “AR ConnectNow” a state-wide hotline for non-emergency crisis services including on-call counselors capable of providing treatment referrals for addiction. OptiMAT would repurpose AR ConnectNow resources through its resources section as well as GEMA intervention, described below. Additional resources include 9-1-1 and up to 3 supportive contacts of the participant’s choice (their “support network”).*(4) Geographic ecological momentary assessment (GEMA)*. Each OptiMAT participant will provide up to three physical locations where they report greatest risk for opioid use relapse. The research coordinator will program each location as a “hotspot” using latitude and longitude coordinates. For privacy purposes, addresses will be identified as the nearest street intersection rather than specific people or places. OptiMAT will create a “geofence” around each hotspot location. The default geofence is a 1/16th mile radius (~300 feet) around the hot spot, but this is adjustable based on urbanicity, rurality, or participant’s privacy concerns. Entering the geofenced perimeter triggers a push notification urging the participant to leave the hotspot. Remaining in the hot spot for 5 min triggers a second push notification asking the participant to report their craving intensity on the sliding bar Likert scale. Remaining in the hot spot for an additional 5 min (10 min total) prompts the participant to call a contact from their support network.*(5) Data security and confidentiality.* Given the sensitive nature of self-reported smartphone data for this project, OptiMAT employs the following security features to ensure participant confidentiality. First, all data will be stored on a HIPAA-compliant, HITRUST-certified secure database managed by Enqbator. Second, data collected by OptiMAT will only be stored temporarily on the phone until the phone detects a secure network (a trusted Wi-Fi or satellite network), at which point data will be uploaded to the above server and erased from the phone. Finally, participants will be required to enable passcode protected screen lock on their phones to prevent unauthorized access.

#### Criteria for discontinuing or modifying allocated interventions {11b}

Participation in this study is voluntary, and participants may withdraw from this study at any time. Study investigators will not collect any new data from participants who withdraw but will retain any data already collected. Participant who withdraw from the study will not be allowed back into the study at a later date.

The principal investigator ([name]) may withdraw participants from the study if (1) they do not follow study instructions, (2) they provide misleading or false information during study assessments, or (3) the principal investigator determines it is not in their best interest to continue. Note that we are documenting daily app usage and missed urinalysis test, so participants not using the app or missing clinical appointments are not valid reasons for withdrawing them from this study.

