#### Outcomes {12}

##### Primary outcome

The RCT has one primary outcome variable: percentage of clinically acquired urinalysis tests negative for opioid misuse. Urinalysis drug testing will consist of solid-phase enzyme immunoassay with positive tests analyzed by LC-MS for metabolite quantification. Urinalysis will assess opioid misuse, defined as presence of opioids in the urine other than Suboxone and its metabolites, including methadone, fentanyl (11 metabolites), oxycodone, phencyclidine, propoxyphene, and buprenorphine or norbuprenorphine, as well as other drugs of abuse including amphetamines, barbiturates, ethanol, benzodiazepines, THC, and cocaine (benzoylecgonine). Urinalysis drug tests will be acquired at each clinical visit, which occur weekly when participants initiate treatment but may occur less frequently (e.g., every 2 weeks) as participants maintain sobriety. We will calculate percent negative urinalysis tests out of total possible urinalysis tests to generate a Treatment Effectiveness Score (TES) describing participant outcome relative to other participants in the RCT [22]. Note that TES treats missed urinalysis tests as positive urinalysis results, thus accounting for treatment cessation. TES also accounts for the frequency of urinalysis tests, which varies as patients matriculate from phase I (weekly) to phases II–IV (biweekly to monthly) as patients demonstrate continued abstinence from opioid misuse.

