### Data collection and management

#### Plans for assessment and collection of outcomes {18a}

The primary outcome variable, quantitative urinalysis drug testing, will be acquired and analyzed by clinical staff per standard clinical procedure (see the “Primary outcome” section).

The secondary outcome variable time to opioid lapse will be derived from quantitative urinalysis drug test results above. The secondary outcome time to treatment discontinuation will be calculated from clinical staff as the first of three consecutively missed clinical appointments. The secondary outcome self-reported days of opioid misuse will be calculated from the monthly time-line follow-back calendar assessments, collected via phone by research staff.

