#### Data management {19}

These data will be stored in patients’ electronic medical records (EMRs). All other surveys and instruments will be administered by research staff using REDCap (Research Electronic Data Capture) database, a secure web-based database for collecting and storing survey-based research data [27]. REDCap includes logic to detect incorrect data entry such as range check for data values. Research staff will manually enter urinalysis results from EMRs into REDCap with double data entry. For privacy and confidentiality, the REDCap database will store information by coded study ID without PHI linkages.

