#### Plans for collection, laboratory evaluation, and storage of biological specimens for genetic or molecular analysis in this trial/future use {33}

Urine specimens will be collected for quantitative urinalysis of opioid misuse. Note that these urine specimens are collected by clinical staff as part of routine clinical care and are not collected specifically for this trial. Urinalysis results will be recorded in participants’ medical records and shared with research staff per study protocol (see Supplementary materials). Urine samples are destroyed following quantitative urinalysis.

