Survival analyses will be performed using the Kaplan-Meier method to compare the study arms on secondary outcomes (1) time to opioid lapse and (2) time to treatment discontinuation. Loss to follow-up will not be coded as relapse and will thus be censored in the Kaplan-Meier survival analyses for opioid lapse but will be coded as treatment discontinuation. As with the analysis above, stratification variables (Site, Chronic Pain, and Comorbid Alcohol or Marijuana Use) will be included in the survival analyses only first. Then, covariates identified above will be added and results will be compared. All analyses will be performed using SAS 9.4.

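### The rule that ends all data collection at study withdrawal also shuts off routine clinic records, so urinalysis and attendance that still exist are lost to the outcomes

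*Protocol article*

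**What the plan says.** **Withdrawal.** Section {11b} of the protocol article states: "Study investigators will not collect any new data from participants who withdraw but will retain any data already collected". The same section lets the principal investigator end participation: that person "may withdraw participants from the study if (1) they do not follow study instructions", or for false information, or on a best-interest judgement. No different data rule is given for these cases. The section then adds that not using the app and missing clinic appointments are not valid reasons for withdrawing someone.

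**Source of the data.** Section {18a} says the urinalysis "will be acquired and analyzed by clinical staff per standard clinical procedure". Section {33} says "these urine specimens are collected by clinical staff as part of routine clinical care and are not collected specifically for this trial". Section {19} gives the route into the database: "Research staff will manually enter urinalysis results from EMRs into REDCap with double data entry".

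**Primary outcome.** Section {12}: "We will calculate percent negative urinalysis tests out of total possible urinalysis tests". A missed test counts as positive, and the stated reason is that this captures people who stop treatment.

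**Missing data.** Sections {20a} and {20c} plan multiple imputation if much is missing at random, and Bayesian models if it is not.

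**Treatment discontinuation.** Section {18a} dates it to the first appointment in a run of three missed at the clinic. The survival paragraph of {20a} censors loss to follow-up in the lapse analysis, "but will be coded as treatment discontinuation" in the other.

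**The concern.** Leaving the study and leaving treatment are different events. The monthly calendar calls need the participant's cooperation, so they must end at withdrawal. Urinalysis and attendance do not: the clinic generates them for its own purposes, and research staff only transcribe them. A participant who wants no more study contact but continues MOUD goes on producing the primary outcome, and the trial stops reading it.

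Three things are at stake. First, obtainable primary-outcome data are lost, and analysis cannot restore results that were never extracted. Second, if the missed-equals-positive rule is applied to those tests, a person still in treatment is scored as though treatment had ceased. Third, such a person could be entered as a treatment-discontinuation event while still attending the clinic.

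Some of this rests on a judgement by someone who knows the allocation. Section {17b} says only laboratory staff and the biostatistician are blinded, and the principal investigator decides on investigator-initiated withdrawal.

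**Working it through.** **1. The plan's own figures, for context.** Inputs from {14}: standardised effect 0.35, type I error 0.05 (two-sided assumed), power 0.80, 20% drop-out, 12 strata.

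- The normal approximation gives 129 per arm, 258 in total. The exact t-test gives 129.1, so 130 per arm, 260 in total, with power 0.803. This reproduces the plan's 260.
- 260 / 0.80 = 325. Rounded up to equal strata, 28 × 12 = 336. This reproduces the enrolment target.
- 0.20 × 336 = 67.2. The plan does not split this drop-out into people who leave the study and people who leave treatment, so it does not give the number affected here.

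None of these figures is in dispute.

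**2. A participant who leaves the study midway and still attends the clinic, under each rule.**

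| Rule | Consequence |
|---|---|
| {11b}, no new data | Later urinalysis and attendance are not extracted |
| {12}, missed counts as positive | If applied, later tests are positive, although its reason (treatment cessation) is absent |
| {20a} and {20c}, missing data | If applied, later tests are imputed or modelled |
| {18a}, three missed appointments | Not a discontinuation |
| {20a}, loss to follow-up | A discontinuation, if a withdrawal is handled as loss to follow-up |
| {20a}, time to lapse | Censored, if handled the same way |

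Rows 2 and 3 compete for the same tests, and rows 4 and 5 give opposite answers for the same person.

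**3. Effect on one participant's TES if row 2 applies.** Let p be the share of tests that are negative, the same before and after withdrawal, and u the share of possible tests that fall after withdrawal. The recorded score is p × (1 − u), so the loss is p × u. Assumptions not in the document: p = 0.70 and exit at week 13 of 26.

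- Weekly testing throughout: u = 13 / 26 = 0.50. The loss is 0.70 × 0.50 = 35 points (70% becomes 35%).
- Weekly, then every two weeks after week 13: possible tests = 13 + 6.5 = 19.5, so u = 6.5 / 19.5 = 0.333. The loss is 0.70 × 0.333 = 23 points (70% becomes 47%).

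Sections {11a} and {12} describe visits thinning out as abstinence continues, down to monthly; monthly testing would make the loss smaller again. The result also depends on p and timing. With weekly testing and exit halfway, 60% becomes 30% and 80% becomes 40%. With p = 60%, exit at one quarter or three quarters of follow-up records 15% or 45%.

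**4. Effect on the arm comparison.** If a fraction w of an arm leaves in this way, that arm's mean falls by w × p × u. Using the two results above, each percentage point of w lowers the mean by 0.01 × 23 = 0.23 to 0.01 × 35 = 0.35 points.

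- Equal w in both arms shrinks a true difference by the factor 1 − w × u. With u = 0.50, w = 10% shrinks it by 5% and w = 20% by 10%.
- Unequal w adds a spurious difference equal to the gap in w times p × u.

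The document gives neither w, nor its split by arm, nor a standard deviation of the TES in points. This step therefore cannot be completed from the plan.

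**The case against.** The strongest reply is that {11b} already limits the problem. Someone who stops using OptiMAT stays in the study, and their urinalysis is still read. That stands. It rules out app non-use as a ground, and with it the most obvious route by which the investigator's decisions could differ between arms. What remains is voluntary withdrawal, false information, best-interest decisions and any other study instruction.

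Second, no passage says that a test taken and recorded, but not extracted, is a missed test. That also stands: a reader might infer that the plan scores these tests as positive, but the text leaves the matter open, with imputation as a rival rule.

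Third, a reader might infer that people who leave the study become treatment failures. The documents do not support this. The TES is a percentage that keeps results from before withdrawal, and in the lapse analysis loss to follow-up is censored.

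Fourth, a reader might take the 67 expected drop-outs as the number affected, or convert an assumed gap between arms into a share of the planned effect. Neither follows. The 20% is not defined as study withdrawal, and people who also leave treatment lose no negative tests through this rule.

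Fifth, the consent materials are supplementary and not shown, and may already deal with continued use of records. That is possible. Even so, the article's own sentence is unqualified and should agree with them.

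**Conclusion.** The concern holds in a limited form. As written, {11b} ends extraction of routine clinic records for anyone who leaves the study, including those who stay in MOUD, and so gives up primary-outcome data that exist and would be cheap to obtain. How post-withdrawal tests enter the TES is ambiguous between scoring as positive and imputation. Sections {18a} and {20a} contradict each other on treatment discontinuation for a study leaver who still attends the clinic, if that person is handled as lost to follow-up; this needs reconciling whatever the size of any bias.

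The size of the bias cannot be derived from the document. The loss of about 23 to 35 points applies to one participant, and only if that person leaves halfway, stays in care with an assumed 70% negative tests, is tested weekly or moves to two-weekly visits, and has unread tests counted as positive. Differential withdrawal between arms is possible, because the app arm carries more study activity and the investigator is not blinded, but the document does not show that it will occur. This is a worthwhile, inexpensive improvement rather than a fatal fault.

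**What to change.** 1. In {11b}, separate stopping the app or study contacts (calls, interviews) from revoking authorisation to use clinic records.
2. Unless authorisation is revoked, continue extracting urinalysis and attendance from the medical record to month 6, including after investigator-initiated withdrawal.
3. State that all randomised participants are analysed as randomised. For those who do revoke authorisation, say which rule governs later tests: missed counts as positive, or the missing-data methods.
4. Reconcile the survival paragraph of {20a} with {18a} so that treatment discontinuation is coded from clinic records, and loss of study contact alone is not an event.

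The cost is a change to the consent and authorisation wording and an IRB modification. Participants must be asked explicitly whether access to their records may continue, and some will decline. Extraction itself is already planned under {19}.

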#### Strategies to improve adherence to interventions {11c}

OptiMAT will send daily reminders for participants to log their daily self-monitoring assessment. Additionally, study staff will review mean OptiMAT use (percent days per month) at each of the participants’ monthly follow-up visits and provide strategies to maintain consistent OptiMAT use.

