##### Secondary outcome

The RCT will have several secondary outcome variables: self-reported days of opioid misuse, time to opioid lapse, and time to treatment discontinuation. Self-reported days of opioid misuse will be assessed using the TimeLine Follow-Back Calendar (TLFB) [23]. The TLFB is a calendar that provides cues (such as holidays) to prompt participants to recall days of opioid misuse over the past month. TLFB will be administered at study enrollment (baseline) and monthly by phone to record opioid misuse over the 6-month RCT. TLFB offers more granularity for days-per-month of opioid misuse than a quantitative urinalysis test but is subject to misreporting. Days of opioid misuse will be collected monthly in the 6-month study.

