#### Procedure for unblinding if needed {17b}

N/A. Only clinical (laboratory) staff and the biostatistician are blinded. We foresee no circumstances in which unblinding of these staff and investigator are permissible.

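### An unblinded, discretionary rule lets randomised participants be withdrawn for false reports, so removal can depend on outcome and arm, and outcome collection may stop with it

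*Protocol article*

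**What the plan says.** Section {11b} of the protocol article gives the principal investigator three grounds for withdrawing a participant from the study. The second is that "they provide misleading or false information during study assessments". The article gives no threshold for falsity, no blinded review, and no limit to falsehoods found before randomisation. The same section states that "Study investigators will not collect any new data from participants who withdraw but will retain any data already collected". It protects one kind of behaviour: "participants not using the app or missing clinical appointments are not valid reasons for withdrawing them from this study". A false report has no such protection.

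On blinding, {17b} says "Only clinical (laboratory) staff and the biostatistician are blinded". The principal investigator also transcribes the allocation orders ({16c}) and presents unblinded interim results to the monitoring board ({21b}).

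On self-report, the app arm reports every day: "Participants will be asked to complete daily assessments of (a) opioid use" (Base features). Section {11c} uses the same term: "OptiMAT will send daily reminders for participants to log their daily self-monitoring assessment". Both arms give the calendar report: "TLFB will be administered at study enrollment (baseline) and monthly by phone to record opioid misuse over the 6-month RCT" (Secondary outcome). The article says that this report offers finer detail than urinalysis "but is subject to misreporting".

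**The concern.** Opioid use is a central self-report in this trial, and urinalysis can contradict it. Research staff enter the urinalysis results into the study database (Data management {19}), so the study team can see a denial that conflicts with a positive test. A participant whose tests are all negative cannot be caught out in this way, whereas one who misuses opioids can. The ground for removal can therefore be a consequence of the outcome.

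The person who decides can know the arm, and one arm produces more statements that might be judged false. Removal after randomisation that depends on both outcome and arm breaks the protection that randomisation gives. If follow-up ends as well, TLFB days after that point are never collected, and no later analysis can restore them. Time to lapse would be censored for a reason related to lapse, since the survival analysis censors loss to follow-up.

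**Working it through.** **The plan's own figures.** For a standardised difference of 0.35, two-sided alpha 0.05 and power 0.80, the normal formula gives n = 2(1.96 + 0.84)² / 0.35² ≈ 128, or 129 per arm with unrounded quantiles. The exact t-test gives 129.1, so 130 per arm and 260 in total, as stated. Enrolment is 260 / 0.80 = 325, and the next multiple of 12 is 336, as stated. This point does not affect these figures. They supply only the arm size and the yardstick below.

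**How uneven could withdrawals be between arms?** Assume equal misuse in both arms.
- App entries not counted as study assessments: both arms have the TLFB only, so the app arm's share is 50%.
- App and TLFB as two instruments, each with independent detection chance p: the app arm has 2p − p² and control has p, so the share is (2 − p)/(3 − p). At p = 0.05 this is 1.95/2.95 = 66%. At p = 0.50 it is 1.5/2.5 = 60%.
- Every entry as a separate chance: 26 weeks × 7 = 182 app entries plus 7 TLFB occasions is 189, against 7 in control. The share is 189/196 = 96%.

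**What happens to the Treatment Effectiveness Score (TES)?** The documents give no withdrawal rates, no variance and no rule for tests after investigator withdrawal. The following are therefore assumptions: no true effect; 130 per arm; 26 tests; individual chance of a negative test distributed Beta(1.2, 0.8), with mean 0.60 and variance 0.08; withdrawal halfway with probability w(1 − p)/0.40, where p is now that individual chance; 1,500 simulated trials per scenario.

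| Withdrawn, app/control | Withdrawn excluded: bias, type I error | Later tests count as positive: bias, type I error |
|---|---|---|
| 5% / 0% | +1.0 points, 6% | −0.9 points, 7% |
| 10% / 2% | +1.8 points, 8% | −1.6 points, 8% |
| 15% / 3% | +2.8 points, 11% | −2.5 points, 11% |

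A positive sign favours OptiMAT. With full follow-up, or with only the tests up to withdrawal, bias was about zero and type I error about 4-5%. The second of these relies on each person's chance of a negative test staying constant over time.

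**Check by formula.** E[p²] = 0.08 + 0.36 = 0.44, so E[p(1 − p)] = 0.60 − 0.44 = 0.16. The mean negative rate among those withdrawn is 0.16/0.40 = 0.40.
- Later tests positive: shift = excess × 0.5 × 0.40. Excesses of 5, 8 and 12 points give 1.0, 1.6 and 2.4 points.
- Exclusion: the arm mean becomes (0.60 − 0.40w)/(1 − w). For 5/0% this is 0.6105 − 0.6000 = +1.05 points. For 10/2% it is 0.6222 − 0.6041 = +1.8. For 15/3% it is 0.6353 − 0.6062 = +2.9.

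Both agree with the simulation. The Monte Carlo standard error of a 5% rejection rate is √(0.05 × 0.95/1500) ≈ 0.6 points, so the 6% entry is hardly distinguishable from 5%, while the 11% entries clearly are.

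**Yardstick.** The SD of the individual chances is √0.08 = 0.283, and 0.35 × 28.3 ≈ 10 points. A bias of 1 to 3 points is about a tenth to three tenths of the planned effect on this assumed scale.

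**The case against.** The strongest reply is that much of this is inference. The rule says the investigator may withdraw, not must. It does not mention opioid use or discordance with urinalysis, and the article treats TLFB misreporting as an expected limitation. The exemption for app non-use and missed appointments already removes the most obvious grounds related to arm and outcome. All of this is fair. It means that the frequency is unknown, not that the rule is safe: nothing in the text excludes the natural trigger.

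A reader might infer that such withdrawals fall mostly on the app arm, setting some 180 daily entries against a few calls. The documents do not support that as fact. The TLFB is itself a day-by-day calendar, and urinalysis exposes denials in both arms, so the number of contradictions is limited largely by urine tests. GPS shows presence at a named hotspot and contradicts no statement by itself.

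A reader might also infer that self-reported days of misuse would be biased in OptiMAT's favour because concealed users leave that arm. That does not follow. Someone withdrawn for denying use has been reporting few days, so removal could raise the arm's mean reported days.

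Finally, the sentence ending data collection stands in the paragraph on voluntary withdrawal, and urinalysis is routine care. Continued collection after investigator withdrawal is therefore not clearly ruled out. That stands, but no provision secures it either.

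**Conclusion.** The point holds as a weakness in a stated rule. An unblinded investigator has discretion to remove randomised participants on a ground that can depend on outcome and on arm, and the only follow-up rule given would end outcome collection. The sign of the TES bias is undetermined because {11b} does not say how tests after investigator withdrawal are treated. Counting missed tests as positive works against OptiMAT if withdrawals are more frequent in its arm, and excluding the participants works in its favour. The size, roughly 1 to 3 points with type I error of about 6-11%, rests wholly on the assumed withdrawal rates, timing and score distribution. If few or no such withdrawals occur, or if they are balanced between arms, little or no bias in the arm comparison follows. The rule should be changed because the protection is cheap and TLFB data not collected cannot be recovered.

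**What to change.** State four things in {11b}:

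1. After randomisation, a discrepancy between self-report and urinalysis is recorded as data and is not by itself a reason to end follow-up.
2. Withdrawal by the investigator does not end collection of routine clinical urinalysis results or of the TLFB, unless the participant withdraws consent.
3. All randomised participants are analysed.
4. Investigator withdrawals are reported by arm and reason.

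This takes a few sentences in the protocol and an instruction to staff. Urine testing is already part of routine care, so keeping those results adds little work, and the TLFB calls are already scheduled. The small downside is that some unreliable self-reports stay in the dataset.
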